**19.6 Study Monitoring**

The study will be conducted in accordance with the principles of Good Clinical Practice (GCP) as laid out in the Indian Council of Medical Research (ICMR) 2017 guidelines, International Conference on Harmonization (ICH) 2017 guidelines on GCP and clinical studies and AYUSH/CCRAS guidelines for Ayurveda research (63-69).

The investigator should ensure that sufficient time is allocated for monitoring activities and for the monitor to meet the appropriate site personnel. The sponsor will arrange monitoring visits to each of the participating centers for evaluating the progress of the ongoing study and identify any unexpected problems/difficulties. During these visits special emphasis will be on checking the study documents.

During the monitoring visits, study monitor will:

1. Examine all source data and CRFs for the correctness and consistency of data, protocol compliance and possible adverse events
2. Discuss inconsistencies in the study data or missing data
3. Ensure that the study medication is correctly stored, dispensed and accounted for.
4. Verify information on the CRFs against source data and proper capturing of the Adverse Events
5. Check adherence to the obligations of the investigator (for documentation and reporting)
6. Review consent forms, in particular the date of consent and signature

Source data will include Case Record Forms and/or copy of any other medical records from hospital and/or referral practice considered relevant by the study investigator. Such verification is an essential element of the Quality Control, as it allows the correction of transcription errors and omissions.

An independent Data Safety Monitoring Board (DSMB) will established to evaluate the data on adverse events (AE) at regular intervals. The DSMB may also consider a need for an interim review to ensure participant safety and emerging outcomes.

**19.7 Record Retention**

All documents relating to the study, including the protocol and the local or core data sheets are the confidential property of the Sponsor and should be regarded as such. Unused CRFs should be returned to Sponsor at the end of the study.

The investigator will retain one copy of the study records (e.g., laboratory printouts, ECG printouts, CRF copies, etc.) and the documentation for least 5 years and await instructions of their final disposal from the sponsor. If the investigator retires or changes employment, custody of the records may be transferred to another suitable person who will accept responsibility for those records. Notice of such transfer will be given in writing to the Sponsor

There will be no destruction or unauthorized alteration of any source records or Case Record Forms.

The Principal Investigator will retain all documentation pertaining to this study in the Medical Records Unit for as long as the study treatment is available for human consumption.

**19.8 Other Documentation**

All the investigators will supply the Principal Investigator with the following:

1. A current signed and dated CV for the investigator and his/her entire study team.
2. Documentation of Independent Ethics Committee’s approval. This should be accompanied by the EC working procedures and the EC Membership List. All these documents should be signed by the EC chairperson or designate.
3. Any local laboratory reference ranges used during the study
4. Copy of the EC approved consent forms (English and local versions)

**19.9 Protocol Amendments**

Should any changes be required to the signed final protocol, a protocol amendment must be prepared and agreed by the Investigators and the respective Ethics Committees before implementation.

Deviations from the protocol should only be made in a medical emergency or as a part of the protocol amendment. In an event of a medical emergency, the investigator must notify the Principal Investigator and the appropriate Ethics Committee within 24 hours.

All the amendments to the protocol must be submitted to the appropriate Ethics Committee before implementation.

**19.10 Window Period**

A 3-5 day window period may be allowed in either side of the scheduled visit for exceptional or any other anticipated reasons at the discretion of the investigator.

**19.12 Standardization of study procedures/Standard Operating Procedures (SOP)**

Following the approval of this protocol by the regulatory body, video-based meetings and discussions will take place with the study team members including investigators to fully comprehend this protocol and ensure uniformity in administration of the various clinical and other procedures required to carry out this study. SOP’s specifically targeting these issues in greater detail are prepared and will be sent to the respective study teams. The SOP’s will complement this protocol

# 20. ETHICAL CONSIDERATIONS

**20.1 Declaration of Helsinki**

The study will be conducted in accordance with the Declaration of Helsinki (1964), as amended in South Africa (1996), Edinburgh (2000) and Washington (2002). (Enclosed Appendix T) (68).

**20.2 Ethics Committee**

The investigator must submit this protocol, plus relevant consent forms and a patient information sheet, for independent review by an Institutional Ethics Committee, and the protocol must be reviewed and approved by this Committee before the start of the study. The Ethics Committee should be constituted as per the guidelines issued by ICMR and endorsed by DCGI (63).

The patient enrollment will not start until satisfactory evidence of ethical approval is obtained in writing.

Amendments to the protocol will be submitted for ethical review before implementation.

**20.3 Regulatory clearances:**

The regulatory clearances will be obtained by the sponsor of the study.

All the guidelines and directions described in Declaration of Helsinki, WHO, ICH-GCP (Jan ’97 version) and DCGI, AYUSH (Ethical Guidelines for Biomedical Research on Human Patients) will be followed (63-69).

This protocol will be registered with CTRI after approval from the Ethics Committee.

**20.4 Funding agency/Sponsor:**

Ministry of AYUSH GOI and CSIR GOI are the principal sponsors and funding agency.

**20.5 Informed Consent**

This is prepared along the ICMR guidelines on GCP 2017) (63).

The investigator must explain the study fully to the patient participating in the study. An information sheet giving details of the study will be provided to the patient for study and discussion if any with the investigator. Sufficient time will be given to the patient to make a voluntary decision to participate. Patient will be encouraged to ask questions and clear all doubts in a face to face interview with the investigator. After fully satisfying with the various provisions of the research study the patient will be asked to sign and date the consent form and this will be then be considered as an informed consent. All consent forms should be signed and dated by the investigator. If the patient is unable to read or write, the consent forms should be signed and dated by the investigator and an impartial witness, to indicate that the patient has fully understood the information and has consented freely.

Consent forms will be reviewed retained by the investigator and reviewed by the study monitor.

**20.6 Confidentiality of Patients:**

All the investigators and their research staff will preserve the confidentiality of the patients taking part in this study. Any information revealed to the Institutional Review Board during the course of this study will be considered confidential. All study documents and report forms, laboratory specimens, and other records available to anyone other than the primary investigator and the research staff will be identified by a coded number to maintain the confidentiality of the patient.

# 21. FINANCING AND INSURANCE

AYUSH-CSIR is the sponsor of the study, has sole responsibility of financing the study.

Adequate Insurance will be obtained for the study participants including the study patients for the required duration of time.

AYUSH will provide insurance coverage with respect to any liability caused by the investigational products and or study related procedures in connection with the clinical study. The terms and conditions will apply as specified in the insurance policy document.

The quantum of compensation for the Serious Adverse Events leading to the death will be given to the patient’s nominee as per recommendations of the EC, DSMB and CDSCO’s expert committee and as per current applicable regulatory guidelines (69).

# APPENDIX

## Appendix A: Schedule of Events

**Table 1: SCHEDULE OF EVENTS:**

| VISIT | Baseline | D 4 | Day 4 Discharge | Discharge | Week 4 | Week 8 | Week 12 | Remarks |
| --- | --- | --- | --- | --- | --- | --- | --- | --- |
| Informed Consent,  Selection Criteria, Demographics, Disease Features, Baseline Symptoms | X |  |  |  |  |  |  |  |
| Medical History and Comprehensive Physical Examination | X |  |  | X |  | X | X |  |
| Symptom, Vital Parameters | X |  |  |  |  |  |  |  |
| Adverse Events **^a^** |  | X | X | X | X | X | X | X |
| AyurvedicEvaluation**^b^** | X |  | X |  | X | X | X |  |
| Pulse Oximetry**^c^** | X | X | X | X | X | X | X |  |
| USG Abdomen and Pelvis | X |  |  |  |  |  |  |  |
| Color Doppler and 12 Lead ECG | X |  |  | X |  |  |  |  |
| Chest X-ray | X | X | X | X |  |  |  |  |
| HRCT Chest | X | X |  | X |  |  |  |  |
| Pregnancy Test | X |  |  |  |  |  |  |  |

| VISIT | Baseline | Day 4 | Day 4- Discharge | Discharge | Week 4 | Week 8 | Week 12 | Remarks |
| --- | --- | --- | --- | --- | --- | --- | --- | --- |
| Hb, TLC, DLC, Platelet, Urine ®**^d^** | X |  | X |  | X | X | X |  |
| ESR and CRP**^e^** | X |  | X |  | X | X | X |  |
| LFT, BUN, SrCreatinine**^f^** | X |  | X |  | X | X | X |  |
| Lipid Profile | X |  |  |  | X |  | X |  |
| LDH, Ferritin**^g^** | X |  | X |  | X |  | X |  |
| IL-6 Pro-cal**^h^** | X |  | X |  | X |  | X |  |
| CK, BNP, Troponin,  D-Dimer **^i^** | X |  | X |  | X |  | X |  |
| Na, K, Cl, Fe, Zn, Mn, Vitamin D , B12 | X |  |  | X |  |  | X |  |
| Oxidation Biomarkers  -SOD, GSH | X | X |  | X |  |  | X |  |
| Cytokine Panel**^J^** | X |  |  | X |  |  | X |  |
| Serum Immune Response**^k^** | X | X | X | X | X | X | X |  |
| Health Related-Behaviour Fitness (HR-BHF) VAS questionnaire, Self Reported Questionnaire (Mobile app)**^L^** | X | X | X | X | X | X | X |  |
| Dispense study medication**^m^** | X |  |  |  |  |  |  |  |
| Completion report |  |  |  | X |  |  | X |  |

Footnotes:

1. Symptom Assessment, vital parameters and monitoring of adverse events to be performed daily by Physician
2. Daily Ayurvedic Monitoring till discharge by Ayurvedic Physician and subsequently for 4, 8 and 12 week.
3. Pulse oximetry to be performed daily

d-f: These tests should be performed at Baseline and once in 3 days till discharge and in addition as per discretion of the treating physician

g-iThese tests should be performed at Baseline and once in 3 day till discharge, week 4 and week 12 and in addition as per discretion of the treating physician

j Cytokine Panel includes IL-2, Il-4, IL-6, IL-10, TNF-α, IL-1β, IL-13, MCP, Gamma Interferon, to be performed at Baseline, Day 5, Day 10, Day 15

Day 20/Discharge, Week 8, Week 12.

k. Serum Immune Response includes IgG, IgM, and will be performed at Baseline, Day 2, Day 4, Day 6, Discharge, Week 4, Week 8, and Week 12.

L .Health Related -Behaviour Habit Fitness , HR-BHF, WHO-QOL Bref, Mobile Application for recording COVID-19 symptoms daily

m. Study medication will be dispensed every 4 weeks, at baseline, week 4 and week 12

Note:

i)The treating physician can ask for any investigations anytime, if need arises and as per clinical judgement

ii)If the discharge takes place within 2 weeks of a particular timeline (week 4 or week 8) then the events/investigations for that particular timeline will merge with those required at time of discharge (DO NOT repeat again for that timeline)

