**e. Study duration:**

The total duration of the study is 12 weeks – this includes a period of hospital based treatment followed by a post recovery period. The Ayurvedic drug will be prescribed as per protocol for a total duration of 12 weeks.

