6. Patients suffering from severe COVID-19 Disease as described above in Section 10.1 and judged by a physician; further guidance can be taken to exclude patient in a clinical context of progressive respiratory dysfunction and failure from the following criteria (i) Respiratory distress at room ambience (≥30 breaths per min) (ii) Oxygen saturation at rest ≤93% (peripheral digital arterial oxymetry) and requiring oxygen support for over one hour to normalize (iii) Any of the known COVID-19 complications and emergency procedures which may require shift/admission in intensive care unit such as respiratory failure, adult respiratory distress syndrome, requirement of oxygen support for over 1 hour, requirement of mechanical ventilation, septic shock, or severe non-respiratory organ dysfunction or failure.(62)
   (Adapted and modified from the reference: Yang Liu et al.Lancet Infect Dis 2020 , March 19, 2020 https://doi.org/10.1016/ S1473-3099(20)30232-2)
7. Chronic, Severe, Unstable, Uncontrolled co-existent medical illness such as Diabetes, Hypertension, Cardiac disorders, liver, kidney disorders and lung disorders or other disease of concern which may put the patient at increased risk during the study
8. History of immunosuppression: solid organ or bone marrow transplant, use of immunosuppressive antimetabolic and biologic agents, intrinsic immunodeficiencies, HIV infection.
9. Active cancer diagnosis, on palliative treatment or requiring current therapy with antimetabolic agents, immunotherapy or radiotherapy.
10. Patients on parenteral nutrition
11. Patients with known sensitivity or contraindication to any of the ingredients of study medication
12. History of bleeding haemorrhoids, haemoptysis, acid peptic diseases, ulcers and pulmonary diseases (tuberculosis, asthma, etc)
13. Patients who are likely to worsen or planed ICU admission or ventilator support due to any reason
14. Pregnancy and lactation
15. Participation in a drug interventional clinical drug trial of any nature in the three-month period preceding onset of COVID-19
16. Participation in any other clinical trial of an experimental agent treatment for COVID-19
17. Patients on any kind of Ayurveda treatment or any other alternative and complementary medicinal systems such as Homeopathy, Unani, Siddha and in particular requiring oral therapy of any kind
18. Patients receiving any other test drug, apart from SOC.

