# 13. LABORATORY & OTHER INVESTIGATIONS

These are common to the each of the three Ayurveda formulation drug trials:

1. Blood/Serum (routine): Haemogram, Platelet count, Total leukocyte differential count, Hemoglobin and ESR, Blood sugar level (Fasting), Liver function test and Liver Enzymes (SGOT,SGPT, Alkaline Phosphatase), Renal functions (Serum creatinine, Blood Urea Nitrogen), Lipid profile (Total cholesterol, HDL cholesterol, LDL cholesterol, Triglycerides, VLDL)
2. Serum (inflammatory markers, organ damage):C-Reactive protein titer, lactate dehydrogenase, ferritin, Pro-Calcitonin, Troponin, D-Dimer,
3. Special tests: Blood for Vitamin D, Vitamin B12, Oxidation Biomarkers (Superoxide Dismutase (SOD), Glutathoine (GSH)
4. Cytokine Panel: Interleukin (IL) IL-2, IL-1 beta, IL-4, IL-6,IL-10, IL-13, IL-17, TNF-α, Monocyte Chemotactic Protein-1 (MCP), Interferon gamma, TGF-bet
5. Serum Protective Antibody Response: IgM and IgG against SARS-CoV-2
6. Routine Urinalysis, Urine Pregnancy Test for women of child bearing potential
7. Confirmatory Diagnostic Test: Nasal and/or Throat swab for real time RT-PCR for SARS-CoV-2 (See Appendix O)
8. Other Investigations: USG Abdomen and Pelvis, ECHO-Color Doppler and 12 Lead ECG

Chest X-ray, HRCT scan Chest

**13.1** Rationale for Cytokine Assay: Cytokine assay can be used to study important anti-viral effects (gamma interferon), immune mediated inflammation (IL-6, anti-TNF, IL-17), TH 1 and TH 2 immune response and antibody producing B cell activity (Il 4, IL 13), activation of immune cells such as macrophage activation (MCP). Intense up regulation and elevation of IL 6 and several other cytokines has been reported by several clinical case series and research in COVID-19 and can guide specific therapy (as in case of use of monoclonal antibody to IL-6 receptor being used to treat Cytokine storm in COVID 19).

Detail methods for diagnostic tests, serology and cytokine assay are described in Appendix O.

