15.5. Visit 4 (week 4)

|  | Symptom Assessment, Vital Parameters |
| --- | --- |
|  | Brief Ayurvedic Evaluation |
|  | Laboratory work up |
|  | Pulse Oximetry |
|  | Monitor Adverse Events |
|  | Health Related-Behaviour Fitness (HR-BHF) VAS questionnaire, Self-Reported Questionnaire (Mobile app) |
|  | Drug Compliance, Dispense study medication |

15.6 .Visit 5 (week 8)

|  | Symptom Assessment, Vital Parameters |
| --- | --- |
|  | Comprehensive Ayurvedic Evaluation |
|  | Medical History, Comprehensive Physical examination |
|  | Laboratory work up |
|  | Pulse Oximetry |
|  | Monitor Adverse Events |
|  | Health Related-Behaviour Fitness (HR-BHF) VAS questionnaire, Self-Reported Questionnaire (Mobile app) |
|  | Drug Compliance, Dispense study medication |
|  |  |

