**Reason for early cessation of study :**

Therapy is to be discontinued : [ Please tick √ as appropriate]

□ Therapy refusal/ if a patient withdraws his/her consent.

□ If treatment fails to achieve the desired effect and the investigator considers another therapy to be more effective for medical reasons

□ Significant protocol deviation *

□ Serious adverse event

□ Significant Laboratory abnormality in the opinion of the investigator

□Loss to follow-up

□ Poor compliance*

□ Pregnancy

□ Intercurrent medical problem*

□ Death

* Please clarify in remarks

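### The only scheduled pregnancy test is at baseline; none is scheduled after that before study drug is resupplied at weeks 4 and 8 of a 12-week course

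*Combined protocol and SAP*

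**What the plan says.** **Testing.** In Table 1 the pregnancy row reads "Pregnancy Test | X". The mark is under baseline, all later cells are blank, and the row carries no footnote letter. Section 13 lists "Routine Urinalysis, Urine Pregnancy Test for women of child bearing potential" without a visit or frequency, and the section on clinical evaluation says that laboratory work follows Table 1. The visit lists after baseline in Section 15 name only a general laboratory work-up. Abdominal and pelvic ultrasound is also marked at baseline only.

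**Dosing and supply.** The synopsis states: "The Ayurvedic drug will be prescribed as per protocol for a total duration of 12 weeks". The lists for week 4 (Section 15.5) and week 8 (Section 15.6) both include "Drug Compliance, Dispense study medication". Table 1 footnote m says: "Study medication will be dispensed every 4 weeks, at baseline, week 4 and week 12". The Table 1 row "Dispense study medication" is itself marked at baseline only, so the resupply appears through the footnote and Section 15.

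**Status of pregnancy.** The exclusion criteria in Section 10 list "Pregnancy and lactation". The completion form in Appendix K has a pregnancy tick-box under the line "Therapy is to be discontinued".

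**The concern.** Pregnancy matters in this plan beyond the day of entry: the completion form treats it as a ground for stopping drug during follow-up. Yet the schedule looks for it once, before the first dose. A woman in the Ayurveda arm who conceives after baseline can be given more study drug at week 4, and again at week 8, with no scheduled test first. Section 8 expects most patients to be home within 5 to 15 days of admission, so most of the dosing period is spent outside hospital. The possible consequence is that a pregnancy is recognised later than it could have been, with dosing continuing in the meantime. This concerns patient safety and the completeness of safety data. It has no bearing on the primary endpoints, the type I error rate or power.

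**Working it through.** The plan gives no figure of its own on this point. The check is a count of scheduled tests against supplies, with simple date arithmetic.

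**Inputs**
- Scheduled pregnancy tests: 1 of the 7 Table 1 time points (baseline).
- Length of dosing: 12 weeks (synopsis, study duration).
- Resupply: weeks 4 and 8 (Sections 15.5 and 15.6). Footnote m also says every 4 weeks.
- Visit window: up to 5 days either side (Section 19.10).
- Ayurveda-arm size: 70 per drug trial (Section 5).
- Assumption: each supply covers 28 days, as the 4-weekly interval implies.

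**Step 1: post-baseline supplies with a scheduled test.** By Section 15 (weeks 4 and 8), 0 of 2. By the dates printed in footnote m (weeks 4 and 12), also 0 of 2. The result does not depend on which set of dates is right.

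**Step 2: drug supplied after the only scheduled test.** Total dosing is 12 × 7 = 84 days. Supply at weeks 4 and 8 is 2 × 28 = 56 days. 56 / 84 = 66.7%.

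**Step 3: age of the baseline test at each resupply.** Week 4: 28 days, range 28 ± 5 = 23 to 33. Week 8: 56 days, range 56 ± 5 = 51 to 61. By the end of dosing it is 84 days old.

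**Step 4: what else could detect a pregnancy.**
- The personal diary reviewed at monthly visits (Section 14).
- The daily app and telephone contact, including the option to ask to speak to the investigator (Fig 1, Section 19.3).
- Examination at discharge and at weeks 8 and 12, with a briefer one at week 4 (Table 1, Fig 1, Section 15).
- Any test that the treating physician chooses to order (Table 1, note i).
- Withdrawal for any condition that the investigator thinks could be harmful (Section 9, item 7).

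None of these requires a pregnancy test. The app questions and the Ayurveda follow-up symptom list contain no item on menses or pregnancy. Irregular menses is asked on the baseline form in Appendix H.

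**Step 5: where the added test should be attached.** Note (ii) of Table 1 merges week 4 or week 8 with a discharge up to 2 weeks away. If week 4 is merged with a discharge at day 28 + 14 = 42, the baseline pack has run out at day 28. Either drug lapses for 42 − 28 = 14 days or it is resupplied in hospital before discharge. The same happens if week 8 is merged with a discharge at day 56 + 14 = 70, because the week 4 pack ends at day 56. A test attached to discharge could therefore come after a resupply. A test attached to each dispensing could not.

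**Step 6: gaps after the change.** At nominal times the gap between tests is 28 days. With the window, the longest gap between the week 4 and week 8 tests is 61 − 23 = 38 days. From the week 8 test to the end of dosing it is 28 days, at most 84 − 51 = 33.

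**The case against.** The strongest reply is that the plan breaks no rule of its own. The entry exclusion is served by the baseline test. Sections 9 and 14 do not name pregnancy, and Appendix K is a tick-box form that records why therapy stopped and imposes no duty to test. This stands, and a reader should not infer that the schedule violates a stated requirement.

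A second reply is that safeguards may exist elsewhere. The patient information sheet and consent form (Appendices F and G) were not in the text available for review, and Section 19.12 refers to SOPs that are not included. Contraception, pregnancy-reporting or testing instructions may be in either. This also stands: the documents do not support saying that the trial has no such provision. Table 1 would still be unchanged, and it is the schedule that sites are told to follow for laboratory work.

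A third is that the informal routes in step 4 form a fairly wide net, with daily contact and repeated examination. They do make detection possible. A discretionary test, however, depends on someone already suspecting pregnancy, and nothing requires that question to be settled before more drug is handed over.

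A fourth is that the 67% says nothing about harm. That is right, and it should not be read as a risk or an exposure rate.

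Finally, testing only the Ayurveda arm would make the detection of pregnancy unequal between arms in an open-label trial whose primary objective includes comparing safety. This is a genuine cost of the change, and the fix addresses it.

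**Conclusion.** The point holds. Table 1 schedules one pregnancy test, at baseline, and no scheduled test after baseline comes before the week 4 or week 8 resupply. It would be wrong to read this as saying that no test at all precedes resupply, because the baseline test does; by the two resupply visits it is simply 28 and 56 days old. The supply figures assume nominal visits and 28-day packs.

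The number of pregnancies cannot be estimated, since the documents do not say how many women of child-bearing potential will enrol. They also give no reproductive-toxicity figure for any of the three products, so the size of any harm cannot be stated. The case for change rests on a verifiable gap in the schedule that is very cheap to close. It is best classed as a cheap improvement.

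**What to change.** In the Table 1 pregnancy row, mark weeks 4 and 8 and add a footnote along these lines: in women of child-bearing potential allocated to the Ayurveda drug, a urine pregnancy test is done and its result recorded before every post-baseline dispensing of study drug, nominally at weeks 4 and 8, wherever and whenever the supply is given, including in hospital or at a discharge merged under note (ii).

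No new visit or specimen is needed. Routine urine is already marked at weeks 4 and 8, and Table 1 footnote d has it repeated every 3 days until discharge. A week 12 test at the end of dosing is optional; it would cover conceptions during the last pack.

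**Cost.** Two marks, one footnote and up to 2 strips per eligible woman. The ceiling is 70 × 2 = 140 strips per drug trial, or 140 × 3 = 420 over the three trials, if every Ayurveda-arm patient qualified; the true number will be lower if any are men or are not of child-bearing potential. If equal ascertainment between arms is wanted, test women in the standard-of-care arm at weeks 4 and 8 too, which doubles the ceiling to 280 per trial. Otherwise, report that testing differed by arm.

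The disagreement on dispensing dates between footnote m, the dispensing row and Section 15 is a separate clerical correction. The clinical handling of a positive result is left to the investigators.
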